## 4.2 Screening Phase

Up to 1000 subjects with SCD who are not already receiving specific therapy for PH will be screened with history, physical examination, standard laboratory assessment, Doppler-echocardiogram and 6MW test. Subjects will have a Doppler-echocardiogram with specific and detailed assessment of TRV, diastolic function (e.g., E/A ratio deceleration time), and valvular and systolic function (Appendix A). Medical history, a physical exam and standard laboratory tests including documentation of SS, SC, SD, or  $Sp^{+0}$  thalassemia hemoglobin genotype, HIV testing will be performed, and blood will be collected for DNA, plasma and serum (Appendix E). NT-pro BNP levels and other specialty biomarkers will be run centrally at the NIH. All screening procedures should be performed two weeks after resolution of vaso-occlusive crisis (VOC), ACS event, or acute transfusion. This will create a cohort in which potential subjects for the MIT will be identified. See Table 3 for a complete schedule of screening assessments.

For all subjects identified with a TRV  $\geq 2.7$  m/s, evaluation for possible causes of pulmonary hypertension should be performed as clinically indicated per routine standard of care. Subjects with a history of regular loud snoring and sleepiness, including males with a neck circumference  $>17$  inches and females with a neck circumference  $> 15$  inches should be referred for evaluation of possible obstructive sleep apnea. Subjects newly recognized to be HIV antibody positive during the screening phase should be evaluated for anti-retroviral therapy as per routine standard of care prior to enrollment in the main interventional trial.

In order to monitor AEs that may be associated with the screening procedures, AEs will be collected if they satisfy the following criteria: 1) the AE is temporally associated with any screening phase study procedure (i.e, beginning or worsening after signing the screening informed consent through 7 days after the last screening procedure) and 2) deemed by the investigator to have a potential association with that procedure.

## 4.3 Observational Follow-up Study

All patients who sign informed consent for the Screening Phase are also consenting to participate in the Observational Follow-up Study. Screened subjects will proceed into the Observational Follow-up Study if a) they do not qualify for -or choose not to participate in- the MIT; b) are discontinued for any reason during the MIT or the Open-label Follow-up Phase; or c) complete the Open-label Follow-up Phase.

To the extent possible, sites will contact each OFS subject either in-person or via telephone every 6-12 months through the end of his/her third study year. This cohort will provide natural history data for the duration of the trial. The clinical data to be collected includes vital status and self-report of health care utilization, episodes of ACS or priapism, and initiation/continuation of therapies for SCD or iron overload. See Table 3 for a complete schedule of Observational Follow-up Study assessments.

Any subject in the observational follow-up cohort without an initial TRV  $\geq 2.7$  m/sec who develops apparent pulmonary hypertension detected through routine clinical care will be eligible for re-screening and participation in the MIT while it is still enrolling.

#### **4.4 Main Interventional Trial**

##### **4.4.1 Description of Study Endpoints**

The *primary efficacy endpoint* is the change in 6-minute walk (6MW) distance across the 16 weeks of therapy.

The *secondary efficacy endpoints* include the following:

- Hemodynamic parameters (right atrial pressure; pulmonary artery systolic pressure; pulmonary artery diastolic pressure; MPAP; pulmonary capillary wedge pressure; PVR; cardiac output; mixed venous oxygen saturation; systemic systolic, diastolic and mean pressures; SVR; and body surface area indexed values for cardiac output, PVR, and SVR)
- Left and right ventricular systolic and diastolic function
- NYHA/WHO functional class
- Borg dyspnea score
- Time to clinical deterioration of PH
- Clinical outcomes: number of visits to emergency departments; hospitalizations; reasons for hospitalizations; episodes of acute chest syndrome, number of transfusions
- Quality of Life score (SF-36 for ages 14-adult; Peds-QL for ages 12-13)
- Pain score (BPI)

The *safety endpoints* include the following:

- Vital signs, including blood pressure
- Change in physical examination
- Urinalysis
- CBC
- Reticulocyte count
- Peripheral oxygen saturation by pulse oximetry
- AE monitoring

- Baseline history and interim history (including pain history, pain treatment, respiratory symptoms, inpatient or outpatient evaluations, and management of SCD-related complications)
- Concomitant medications monitoring

The *genetic/biomarker assessments* include the following:

- NT-pro Brain Natriuretic Peptide levels (BNP)
- DNA sequencing

#### **4.4.2 Description of Study**

##### **4.4.2.1 Baseline**

Subjects whose screening data satisfy MIT the inclusion/exclusion criteria will be offered participation in the MIT, starting 2-4 weeks after screening. Although a TRV  $\geq 2.5$  m/s is associated with an increased risk of death in patients with SCD, a TRV  $\geq 2.7$  m/s was chosen to minimize the potential inclusion of patients with false positive (borderline) TRV values. After obtaining informed consent, subjects will be evaluated for additional medical history since screening. They will also participate in a physical examination, baseline laboratory testing, chest x-ray, and a second echocardiogram with documentation of TRV for estimation of right ventricular systolic pressure, assessment of LV systolic and diastolic function, a second 6MW test and Borg dyspnea score for baseline exercise capacity, and assessment of NYHA/WHO functional class. In the case that a subject receives an unscheduled blood transfusion, all study assessments should not be performed until after 2-3 weeks have passed (i.e., 14-21 days). Additional baseline assessments include completion of the Quality of Life assessment and completion of a one-week pain diary composed of daily assessment using the Brief Pain Inventory (BPI). See Table 4 for complete list of baseline assessments.

Subjects will be categorized into 1 of 2 strata, based on their TRV as assessed during the baseline echocardiogram: TRV  $\geq 2.7$ -2.9 m/s and TRV  $\geq 3.0$  m/s.

##### **4.4.2.2 Right Heart Catheterization (RHC) Procedure**

Subjects enrolled in the trial with TRV  $\geq 3.0$  m/s (at least moderate PH) will also undergo RHC (using standard techniques and while the subject is in steady state) at baseline and after 16 weeks. Following premedication, RHC is performed under local anesthesia with a heparin-bonded thermodilution Swan-Ganz catheter inserted percutaneously into the right internal jugular or a femoral vein depending on anatomic landmarks. Catheter is positioned in the pulmonary artery with pressure monitoring. Catheter tip position will be evaluated by fluoroscopy or chest radiography. Fluoroscopy may be used according to standard clinical practice. A 20-gauge heparin-bonded cannula inserted percutaneously into a radial, brachial or femoral artery may be used for blood sampling and monitoring of systemic arterial pressure. Mean vascular pressure levels are determined by electronic integration of the pressure signals. Heart rate and vascular pressures are monitored

continuously. Cardiac output is measured in triplicate by thermodilution or by the Fick method with measured oxygen consumption. Systemic and pulmonary vascular resistances are calculated using the mean cardiac index and mean vascular pressures.

In subjects undergoing right heart catheterization the acute hemodynamic effects of inhaled NO and oral sildenafil will be assessed at rest (see Table 2 and Appendix C) at baseline and at the end of the study.

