### **9.2.2 Right Heart Catheterization**

The pulmonary artery catheter is a triple lumen central venous catheter with two lumens devoted to the pressure transduction functions. The distal port will transduce pressure from the pulmonary artery and from the left atrium, when in the "wedge" position. The central venous port transduces right atrial pressures. During catheter placement, right ventricular pressures are transduced. Pulmonary artery systolic and diastolic pressures, right atrial pressure, pulmonary capillary wedge pressure, systemic artery systolic and diastolic pressures, cardiac output, and calculated systemic and pulmonary vascular resistances will be obtained using this methodology.

Baseline and endpoint RHC procedures should be conducted under similar conditions (e.g., level of sedation and oxygen). Endpoint RHC should be conducted at trough levels of study drug: approximately 4 hours post-dose.

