Now we show that the sample size calculated for the primary endpoint is appropriate for detecting significance in the secondary hemodynamic endpoint (change from baseline PA pressure) using data from the recently completed SUPER-1 trial (a randomized placebo control trial evaluating the effects of 20 mg, 40 mg or 80 mg TID of sildenafil in subjects with PH). Using the hemodynamic data from the 80 mg arm of the SUPER-1 trial with 5% two-sided significance level and 80% power, the N for mean change from baseline PA pressure is 32 subjects per group, for pulmonary vascular resistance the N is 25 subjects per group. Assuming that half of the subjects enrolled in the trial will have moderate to severe PH ( $TRV \geq 3.0$  m/s) and meet criteria for RHC the study will be adequately powered to ascertain the hemodynamic effects of 80 mg sildenafil.

Based on the data described herein, we will randomize 132 subjects into the study (approximately 33 per each of four treatment arm/TRV strata combinations). All randomized subjects will contribute to the primary intent-to-treat (ITT) analysis. Assuming a 15-20 % incidence of PH (defined by  $TRV \geq 2.7$  m/s) in adults with sickle cell disease, approximately 1000 subjects will have to be screened for eligibility to ensure a sufficient number of subjects with  $TRV \geq 2.7$  m/s. Subjects will be stratified and randomized for each TRV stratum and treatment arm ( $\geq 2.7$ - $2.9$  m/s and  $\geq 3.0$  m/s) with 66 subjects assigned to each treatment.

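### Section 4.4.2.2 computes PVR and SVR from cardiac index, which gives the indexed resistances, while Section 4.4.1 lists un-indexed and indexed resistances as separate endpoints

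*Protocol*

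**What the plan says.** Section 4.4.2.2 describes how flow is obtained at catheterisation: "Cardiac output is measured in triplicate by thermodilution or by the Fick method with measured oxygen consumption". The next sentence gives the derivation: "Systemic and pulmonary vascular resistances are calculated using the mean cardiac index and mean vascular pressures".

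The endpoint list in Section 4.4.1 includes "pulmonary capillary wedge pressure; PVR; cardiac output; mixed venous oxygen saturation" and, later in the same item, "SVR; and body surface area indexed values for cardiac output, PVR, and SVR". PVR, SVR and cardiac output are therefore endpoints in their own right, and the indexed version of each is a further endpoint.

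Section 9.2.2 comes back to the catheter measurements and says that "cardiac output, and calculated systemic and pulmonary vascular resistances will be obtained using this methodology". It gives no formula and does not mention cardiac index. Section 11.6 states that "for pulmonary vascular resistance the N is 25 subjects per group", based on external trial data at a "5% two-sided significance level and 80% power".

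**The concern.** Pulmonary vascular resistance is the pressure drop across the lung divided by cardiac output. Dividing by cardiac index gives a different quantity, the indexed resistance. Section 4.4.2.2 applies the cardiac-index rule to both resistances without limiting it to the indexed versions, and no other section supplies a rule for the un-indexed endpoints. Read together with Section 4.4.1, the protocol names two pairs of endpoints and defines only one pair, under the other pair's name.

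At stake is whether the reported PVR and SVR are what their labels say. Haemodynamic change after 16 weeks is a named secondary objective, and PVR is one of two haemodynamic measures given a sample size. With about nine sites, there is also a risk that some follow the sentence and others divide by cardiac output.

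**Working it through.** **The plan's own figure.** The only stated number that depends on PVR is 25 per group. It cannot be reproduced, because Section 11.6 gives no PVR difference, SD or units. Inverting it at two-sided 5% and 80% power gives a standardised difference of (1.960 + 0.842) × √(2/25) = 0.79, or about 0.81 with the t distribution. That value is used below.

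**Algebra.** Let G be the pressure gradient, CO cardiac output and CI = CO / BSA. Then G / CI = (G / CO) × BSA. The same holds for SVR with its own gradient. The rule as written therefore returns the un-indexed resistance multiplied by BSA.

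**Size per subject.** The protocol gives no typical values, so these are assumptions: G = 20 mmHg, CO = 8.0 L/min.

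- PVR = 20 / 8.0 = 2.5 Wood units.
- At BSA 1.7 m², CI = 8.0 / 1.7 = 4.71 and 20 / 4.71 = 4.25.

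| Assumed BSA (m²) | PVR, G / CO | As written, G / CI | Ratio |
|---|---|---|---|
| 1.3 | 2.50 | 3.25 | 1.30 |
| 1.5 | 2.50 | 3.75 | 1.50 |
| 1.75 | 2.50 | 4.38 | 1.75 |
| 2.0 | 2.50 | 5.00 | 2.00 |
| 2.2 | 2.50 | 5.50 | 2.20 |

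The indexed endpoint, computed properly as G / CI, is then the same number as the one labelled PVR.

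**Effect on the arm comparison if all sites use the written rule.** With BSA of mean 1.75 m² and a coefficient of variation of 0 to 15%, simulation gives an absolute difference about 1.75 times larger. The standardised difference goes from 0.79 to 0.78 at most, and power at 25 per group stays at about 79–80%.

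**Effect if sites differ.** Let a fraction p of subjects carry the factor b = BSA, balanced across arms, with the same rule at both of a subject's catheterisations. Take placebo mean change 0, SD 1 in each arm, and treatment effect δ = 0.81.

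- Mean factor: m₁ = 1 − p + pb. Mean squared factor: m₂ = 1 − p + pb².
- Difference = δm₁. Placebo variance = m₂. Active variance = m₂(1 + δ²) − δ²m₁².
- For p = 0.5 and b = 1.75: m₁ = 1.375, m₂ = 2.031, difference 1.114, variances 2.031 and 2.124, so the standardised difference is 1.114 / √2.077 = 0.77.

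| b | p | Power, 25 per group | Power, 33 per group |
|---|---|---|---|
| any | 0 or 1 | 80% | 90% |
| 1.75 | 0.25 or 0.5 | 76% | 87% |
| 2.1 | 0.25 or 0.5 | 73–74% | 84–85% |

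The 33 per group is the approximate number per arm in each TRV stratum given in Sections 4.4.2.4 and 11.6.

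**The case against.** The best defence is that the sentence is loose wording meant for the indexed values. Section 4.4.1 shows that the authors know the difference, Section 4.4.2.2 says that cardiac output is what is measured, and Section 9.2.2 lists cardiac output beside the calculated resistances. Every input for the correct PVR and SVR is itself a listed endpoint, so correct values remain recoverable. This stands as a limit on the consequence: the error occurs only if the sentence is used as written. It does not remove the conflict, because no other formula is given.

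A reader might infer four stronger points that the documents do not support.

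- **Values indexed twice.** Nothing in the protocol instructs anyone to multiply an already indexed value by BSA, and it does not say who computes the resistances or show the data fields.
- **A seriously damaged power claim.** Uniform use costs at most about one percentage point. Mixed use costs about 4 to 7 points at 25 per group and leaves power above 80% at 33 per group under the assumptions shown.
- **A mismatch with the external PVR data behind the 25 per group.** The protocol does not say whether those data were indexed.
- **A fault in allowing thermodilution or Fick.** Section 9.2.2 asks for similar conditions at both catheterisations, and its examples are not exhaustive. Naming the method would be added detail, separate from this error.

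**Conclusion.** The rule in Section 4.4.2.2 is wrong for the un-indexed endpoints in Section 4.4.1. Followed literally, it overstates PVR and SVR by a factor equal to BSA, that is 1.3 to 2.2 times over an assumed BSA range of 1.3 to 2.2 m², and makes the indexed endpoints duplicates. The algebra is exact; the size rests on the assumed BSA.

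The harm is to labels, units and absolute values. Within-subject percent change is unaffected while BSA is stable. The affected endpoints are secondary, come only from subjects with TRV ≥ 3.0 m/s, and carry p-values that Section 11.5.3 treats as descriptive. The primary 6MW analysis does not depend on them.

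**What to change.** Replace the sentence in Section 4.4.2.2 with explicit formulas and units:

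- PVR = (MPAP − wedge pressure) / mean cardiac output.
- SVR = (mean systemic pressure − right atrial pressure) / mean cardiac output.
- PVRI and SVRI use the same gradients divided by mean cardiac index.

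Have the data coordinating center derive all four from the recorded pressures, cardiac output and BSA, so that every site's values rest on one rule. Weight is among the vital signs in Section 9.3.3 and height has a field on the sample intake form in Appendix B; both need to reach the database, as the indexed endpoints already require.

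The cost is one corrected passage and a short central derivation, with no added procedure and no change to sample size.

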**Table 2. Inhaled NO and Oral Sildenafil Challenge at Baseline**

|        | Intervention     | Duration           | Assessment                 |
|--------|-------------------------|---------------------------|-----------------------------------|
| Step 1 | Baseline                |                           | Resting hemodynamics              |
| Step 2 | Inhaled NO 40 ppm       | 10 minutes                | Resting hemodynamics  |
| Step 3 | None                    | 10 minutes                | Resting hemodynamics              |
| Step 4 | Sildenafil 60 mg orally | 30 minutes post oral dose | Resting hemodynamics              |
| Step 5 |                         | 60 minutes post oral dose | Resting hemodynamics              |

 Resting hemodynamics assessed at the end of the 10 minute period of inhaled NO, while the subject is still inhaling the NO.

Right heart catheterization will be repeated at the end of the double-blind phase. This hemodynamic assessment will follow the guidelines below:

- Subjects will take their nighttime dose of study medication, but will not take their morning dose prior to right heart catheterization.
- Subjects will bring study medication to visit.
- Study medication is administered with direct observation by study coordinator
- Right heart catheterization will be performed approximately 4 hours after study medication is administered
- Baseline hemodynamic measurements will be performed as outlined in Table 2 (steps 1-3).
- Blinded study medication will be administered and hemodynamic measurements will be performed at 30 and 60 minutes post dosing as outlined in steps 4 and 5 of Table 2.

If during right heart catheterization, it is not possible to obtain an adequate reading of the pulmonary capillary wedge pressure, a left heart catheterization will be performed for the measurement of left ventricular end-diastolic pressure.

#### **4.4.2.3 Monitoring for Priapism**

Priapism is defined in this study as a sustained, painful erection lasting more than 3 hours or intermittent painful unwanted erections lasting less than 3 hours. Males will be monitored for priapism for 6 hours after sildenafil therapy in the catheterization laboratory (for subjects with TRV  $\geq 3.0$  m/s) or in the clinic after the first dose of study drug during the double-blind phase for subjects with TRVs between 2.7 m/s and 2.9 m/s.

In addition, all male patients will be monitored in the clinic for priapism after their first dose of sildenafil during the open label follow-up phase.

Males will be specifically monitored for incidence of priapism during their study visit interviews. Additionally, they will be instructed to contact a member of the study team at the onset of any degree of priapism and will be admitted for immediate evaluation and treatment. Each site will have a priapism management plan in place. Additionally, the study's Manual of Operations (MOO) will provide possible therapeutic interventions which will be individualized as clinically appropriate for each episode of priapism.

#### **4.4.2.4      *Randomized, Double-blind Phase***

The randomized, double-blind phase of the MIT is designed to test the efficacy of 16 weeks of chronic sildenafil therapy on exercise endurance (6MW distance) and right ventricular systolic pressure (RVSp) in patients with PH and SCD. Randomization of patients meeting inclusion criteria will be stratified in two subgroups according to TRV ( $TRV \geq 2.7$ - $2.9$  m/s and  $TRV \geq 3.0$  m/s); approximately 33 individuals will be randomized to each of the four treatment arm/PH strata combinations.

In the event of VOC, ACS or transfusions, all end-point assessments (including hemodynamic assessment) should be performed  $14 \pm 3$  days after resolution of the acute event or transfusion.

All subjects will have their baseline data confirmed for eligibility prior to randomization. Those qualifying subjects with TRVs between 2.7 m/s and 2.9 m/s will proceed to randomization. Whereas qualifying subjects with  $TRV \geq 3.0$  m/s will next undergo the RHC procedure; those subjects with qualifying wedge pressures will then proceed to randomization. Subjects will be randomized to receive sildenafil 20 mg by mouth (PO) or placebo (matching in pill color and size) three times a day (TID). Study drug will be issued on an outpatient basis for six weeks with the dosage increased to 40 mg TID for four weeks and then increased to 80 mg TID for six weeks.

A peak dose of 80 mg TID was chosen to match our initial open label experience with sildenafil. This is based on the role of hemolysis-associated decreased NO bioavailability in the pathogenesis of pulmonary hypertension associated with sickle cell disease.

The dosing regimen was designed to achieve the following 2 objectives:

1. Minimize sildenafil related adverse effects such as headache and facial/periorbital edema through gradual dose escalation
2. Provide the ability to evaluate the relative efficacy of different sildenafil doses on functional capacity and pulmonary artery pressures as evaluated by echocardiogram

Clinical follow-up will occur at weeks  $6 \pm 1$ ,  $10 \pm 1$ , and  $16 \pm 1$  or EOS, with the following procedures/tests:

- History
- Physical exam and vital signs
- Adverse event monitoring
- Concomitant medications
- Venous blood will be obtained for CBC, standard chemistries
- Pregnancy test
- Venous blood will be obtained for NT-pro Brain Natriuretic Peptide levels and other specialty biomarkers to be run centrally at the NIH
- Emergency department visits, outpatient/day hospital visits and hospital admissions for sickle cell disease and those for complications of PH will be recorded
- Six-minute walk (with assessment of Borg dyspnea index, and NYHA/WHO functional class) 1-2 hours after taking the morning dose of study drug
- Echocardiogram with assessment of TRV LV and RV function 1-2 hours after taking the morning dose of study drug. All echocardiograms should be performed at least one hour after 6MW test. EXCEPTION NOTE: Echocardiogram will not be assessed at week  $10 \pm 1$
- Study drug compliance and daily pain assessment using the BPI --evaluated by subject for one week between each follow-up visit

End of the double-blind phase visit (week  $16 \pm 1$ ) will also include:

- In subjects with an initial study entry TRV  $\geq 3.0$  m/s a second right heart catheterization
- Quality of life assessment using SF-36 Quality of Life form (ages 14-adult) or Peds-QL (ages 12-13)

In subjects with TRV  $\geq 3.0$  m/s clinically indicated studies (according to accepted guidelines) for the work-up of subjects with pulmonary hypertension (PH) can be ordered at the discretion of treating clinicians. These studies could include:

- Collagen vascular screening tests (e.g., ANA, anti-centromere antibodies, anti SCL-70, antiphospholipid antibodies)
- Ventilation perfusion scan
- Chest X-ray (required for all MIT subjects at baseline), CT of chest
- Overnight pulse oximetry
- Spirometry with bronchodilation

- Lung volume
- Diffusing capacity for CO

Efficacy assessments will be done at peak dose (i.e., study medication should be taken 1-2 hours before measurements) when subjects are in a steady state.

A subset of clinical outcomes will be adjudicated by a blinded panel of experts. Adjudicated outcomes include: ACS, right heart failure, and clinical worsening.

Records of study drug used, dosages administered, and intervals between visits are kept during the study. Study drug accountability is performed on an ongoing basis by the study personnel and checked by the clinical research associate (CRA) during site visits and at the completion of the study. Subjects are asked to return all unused study drug at each visit.

To promote treatment compliance, the study personnel will be contacting the study subjects throughout the trial reminding them to administer the study drug as required per protocol. Additionally, subjects will be asked to complete a dosing diary for 1 week in-between each clinic visit.

